## Abstract

**Background:**

Forensic psychiatric patients often suffer from a multitude of severe psychiatric and social problems. Meanwhile multimodal evidence-based interventions are scarce and treatment effectiveness is in need of improvement. The main goal of forensic psychiatric treatment is to address psychiatric and social factors and thereby mitigate criminal behaviour. Notably, a supportive social network is an important protective factor for criminal behaviour. As such, improving a poor social network may decrease the risk of criminal recidivism. This study aims to examine the effectiveness of the addition of an informal social network intervention (FNC) to treatment as usual (TAU) among forensic psychiatric outpatients.

**Methods:**

In a mono-center randomized controlled clinical trial with two parallel groups, forensic psychiatric outpatients with social network-related problems (*N* = 105) will be allocated to either TAU + FNC or TAU alone. The informal social network intervention consists of a 12-month coaching intervention, performed by the forensic network coach (a volunteer trained by an informal care institute). Assessments will be conducted at baseline and 3 months, 6 months, 9 months, 12 months, and 18 months after baseline. The primary outcome variable is mental wellbeing. Psychiatric functioning, criminal recidivism, substance abuse, quality of life, social network, social support, loneliness and self-sufficiency are included as secondary outcomes. A variety of potential mediators and moderators of effectiveness will be explored. Additionally, a qualitative evaluation of effectiveness will be performed.

**Discussion:**

This study will contribute to the existing literature of forensic treatment effectiveness as it is the first RCT examining the effectiveness of adding a social network intervention in a forensic outpatient population. If effectiveness is shown, forensic mental health care could be optimized by collaborating with informal care or community initiatives aimed at improving a positive social network. In addition, results will provide insight regarding mediators and moderators of treatment effectiveness.

**Trial registration:**

This study is registered at the Netherlands Trial Register (NTR7163). Date of registration: 16 april 2018.

## Background

Forensic psychiatric patients often suffer from severe mental disorders, addictions and intellectual disabilities, combined with delinquent behavior [1–4]. In addition, they are confronted with multiple social problems, including housing problems, unemployment, financial problems and social network-related problems [5–8]. Given the complexity of these problems, forensic psychiatric patients are in urgent need of effective treatment. The main goal of forensic psychiatric treatment is to reduce the risk of criminal recidivism. Therefore, forensic psychiatric treatment should be multimodal and personalized; focused on improvement of the social context of the individual patient and multiple mental health problems, related to their delinquent behaviour [9, 10].

Forensic psychiatric treatments that comply with the Risk-Need-Responsivity (RNR) principles are found to be most effective [11]. The RNR-model is used worldwide for the indication and execution of forensic treatments [12, 13]. This model emphasizes that treatment is effective if: 1) the level of treatment intensity is matched to the risk level of criminal recidivism - Risk principle, 2) the criminogenic needs related to criminal recidivism are addressed - Need principle, and 3) the type of intervention is matched to the abilities and skills of the delinquent - Responsivity principle [14]. Forensic assertive community treatment (forensic ACT) and forensic flexible (or function) assertive community treatment (forensic FACT), a Dutch adaptation of forensic ACT [15], are examples of broadly applied multimodal treatment models for forensic psychiatric outpatients [15–17]. In order to prevent criminal recidivism, forensic (F) ACT incorporates the RNR-principles by focusing on multiple individual and systemic risk factors (e.g. financial or cultural barriers, a lack of services) as well as patient’s nonadherence [18–20]. However, there is much variation between individual forensic (F) ACT treatment trajectories and core elements are not well defined [21]. Furthermore, many previous effect studies showed methodological limitations; results from randomized controlled trials (RCTs) are scarce [22]. Overall, the effectiveness of outpatient forensic interventions is limited. A meta-analysis showed positive effects – statistical significant declines of criminal recidivism in the experimental conditions – in only a minority (32.3%) of the forensic interventions [23]. Nevertheless, forensic (F) ACT is a well described and promising multimodal treatment model that meets the complex needs of forensic patients in clinical practice. In order to further improve treatment effectiveness for this vulnerable group, working mechanisms of the current (multimodal) forensic treatments models should be studied extensively. Hence, more RCTs are necessary to develop specific evidence-based interventions [24].

Social network-related problems of forensic psychiatric populations are considered one of the important targets within treatment [25–27]. A substantial part of the social network of forensic patients is engaged in criminal activities or consists of network members with psychiatric problems and substance (ab) use [5, 28]. Also enhanced levels of loneliness are observed in prison and forensic inpatient populations [29, 30]. Both the absence of social support and the presence of a criminal social network of family and friends has been related to increased criminal behavior [31–33]. Indeed, a supportive social network - a network of personal contacts that contribute to a social identity, new contacts and provide emotional, instrumental and material support [34] - has been postulated as an important protective factor against criminal recidivism [35]. As such, strong social support, stable contact with positive peers and social ties with prosocial adults are related to less criminal recidivism rates [35–37].

Until now, systematic reviews showed that social network interventions lead to health behavior improvements in general populations [38]. Among psychiatric populations, social network interventions focused on network-related problems and family relationships, can lead to improved mental wellbeing and a better use of mental health services [39, 40]. Despite these results and the positive influence of social support on criminal recidivism, social support interventions are not actively applied (in addition to treatment as usual) in forensic populations [26, 41]. Moreover, RCTs and other evaluative studies that examine the effectiveness of social network interventions in forensic psychiatric populations are scarce. One pilot RCT that compared a short group social support intervention with a general re-entry service among a small sample of recently released prisoners, found no statistically significant group effects for social support, cognitions, substance use and recidivism [42]. However, larger sample sizes are recommended to reliably investigate the effectiveness of the intervention. Furthermore, the intervention comprised of a short intervention (i.e. 10 week training), while researchers emphasize that social support interventions for forensic psychiatric patients should be long lasting in order to find significant effects [27, 42]. An evaluative study of a social support intervention among mentally ill prisoners during and after incarceration found a significant positive association with quality of life, but no significant association with criminal recidivism or psychiatric hospitalisation [43]. The generalizability of these results is limited due to a small sample size and low treatment adherence rates. Other researchers found some positive results - improved criminal recidivism outcomes - in a group of former prisoners that received social support by community volunteers [41]. The addition of an informal or volunteer-based social network intervention could be promising, since social networks of forensic patients are often overrepresented by formal or professional health caregivers [28]. Improvement of supportive social networks during treatment of forensic psychiatric patients with social network-related problems might reduce criminal recidivism directly or indirectly, for example by enhancing mental wellbeing which may lead to reduced mental health problems and criminal recidivism. More RCTs with a sufficient sample size are needed to examine the effectiveness and working mechanisms of social network interventions in forensic psychiatric populations.

Therefore, in the present study, a randomized parallel-group RCT will be conducted to examine the addition of Forensic Network Coaching (FNC) - an informal social network intervention - to (a multimodal) treatment as usual (TAU) among forensic psychiatric outpatients. The aim of FNC is to: 1) improve (the quality of) social networks, 2) social support, and 3) social participation. To provide an accessible social network intervention and stimulate patients’ adherence to the intervention, FNC will be tailored to the individual needs. To promote effectiveness, FNC is available for a prolonged period of maximum 12 months to promote effectiveness. To our knowledge, this is the first RCT that examines the additional effectiveness of an informal social network intervention within forensic clinical practice. Hence, this study will contribute to generalizable knowledge about the effectiveness of (specific) interventions for forensic psychiatric populations.

### Research aims

The first aim of this study is to examine the effectiveness of the addition of FNC to treatment as usual (TAU) on the mental wellbeing among forensic psychiatric outpatients with social network problems and limited social participation. We expect significantly enhanced mental wellbeing rates in FNC as compared to TAU alone, by improving social networks, social support and social participation. The second aim is to examine the effectiveness of the addition of FNC on psychiatric functioning, criminal recidivism, addiction and other secondary outcomes (quality of life, social network, social support, loneliness, self-sufficiency). We expect significant improvements on psychiatric functioning, criminal recidivism and addiction, as well as on other secondary outcomes, in the FNC condition as compared to TAU. The third aim of this study is to gain insight into the development of the primary and secondary outcomes over time. To enhance knowledge regarding the underlying mechanisms, a variety of potential mediators and moderators will be explored.

## Methods

### Design

A mono-center open label RCT with a two parallel group design will be conducted. A total of 105 eligible participants will be randomly allocated to either TAU with the addition of FNC or TAU alone, after the first baseline assessment. All participants receive treatment as usual within a forensic mental health care institute at the time of the baseline assessment. Participants in the FNC condition are offered an additional intervention – Forensic Network Coaching – consisting of two-monthly appointments with a forensic network coach. Assessments will take place before randomization at baseline and every 3 months after baseline assessment until the final assessment at 12 months of treatment. The follow-up assessment will be conducted at 18 months after baseline assessment. Number of crime occurrences and recidivism rates, will be determined at 12 months and 36 months after baseline assessment*.* The effectiveness of FNC will be examined at 12 and 18 months after baseline assessment. Approval for the study protocol was given by the Medical Ethics Committee of the VU University Medical Center (registration-number NL60308.029.17). The study is registered at the Netherlands Trial Register, part of the Dutch Cochrane Center (NTR7163). Figure 1 provides an overview of the trial design.

**Fig. 1 Fig1:**
[figure not shown]
Overview of the trial design

### Participants

This study is conducted at the outpatient care site of Inforsa Forensic Mental Health Care, specialist in forensic psychiatric care for (young) adults, located in Amsterdam. Inforsa consists of three different forensic outpatient care sites: 1) forensic flexible assertive community treatment (forensic FACT) for adults, 2) forensic FACT for youth and young adolescents, and 3) forensic outpatient clinic. The overall patient population of Inforsa is characterized by complex addiction, psychiatric and personality disorders in combination with delinquent behavior. The type of crimes committed by patients are diverse, most common offences are violence or theft. Treatment is a mandatory part of a conditional sentence, for 87% of the patients. The majority of the patients (69%) suffers from psychiatric or personality disorders in combination with addiction - double diagnoses. On top of that, at least 11% of the patients suffers from intellectual disabilities - triple diagnosis. Most patients have social problems such as housing problems, work problems and financial problems.

Our goal is to include 105 (young) adult forensic outpatients with limited social networks and social participation. Inclusion criteria are: 1) the patient is at least 3 months in treatment at Inforsa and capable of accomplishing appointments according to the primary clinician, 2) the patient is diagnosed with addiction, psychiatric or personality disorder according to the Diagnostic and Statistical Manual of Mental Disorders (Fourth edition, Text Revision and Fifth edition; DSM-IV-TR/5), 3) the patient is aged 16 years or older, 4) the patient is indicated as limited self-sufficient regarding social participation and social network as measured with corresponding items on the Self-Sufficiency Matrix (SSM) [44, 45], and 5) the patient is not completely satisfied with social relationships and the social support as measured with the Manchester Short Assessment of Quality of Life (MANSA) [46]. Exclusion criteria are: 1) acute psychotic symptoms according to the clinician or DSM-IV-TR/5 criteria as measured with the MINI International Neuropsychiatric Interview-plus (version 5.0; MINI-plus) [47], 2) current high risk for suicide requiring immediate intervention according to the clinician and/or DSM-IV-TR/5 criteria as measured with the MINI-plus, 3) severe addiction problems as measured with the Health of the Nations Outcome Scales (HoNOS) [48] requiring immediate intervention or hospitalization, 4) a current high risk for severe aggression towards clinicians or others as measured with the HoNOS, and 5) patient is included in another scientific research project conducted at Inforsa.

### Sample size

As our primary outcome variable is the total mean score on a self-report questionnaire - Mental Health Continuum - Short Form (MHC-SF) [49] - which measures mental well-being using Likert scaling, we consider this outcome as a continuous variable. Normality of the distribution will be checked after data collection using optimal scaling or scatter plotting. When the assumption of normality is violated, resampling methods will be used to transform the data into a normal distribution.

An accurate sample size estimation is challenging since no other studies have been performed with a comparative experimental design and intervention within the same population. Former studies evaluating mentoring programs show small to medium effect sizes [50–53], whereas studies investigating psychological, educational and behavioral treatments show larger mean effect sizes [54]. Effect sizes of life coaching performed in a nonclinical sample show medium to large effect sizes [55]. Given the foregoing, we expect a small to medium improvement of mental well-being in the FNC condition compared to TAU. We consider this a realistic and clinically meaningful effect. Our first power calculations (conducted with G*Power) indicated that 150 participants are needed (75 per arm) to detect a small-to-medium effect size (Cohen’s *f* = .20), given an alpha of 0.05 (two-tailed) and a power of 0.80. Since this power calculation did not account for the repeated measures design of the study, more modern power calculations were performed (conducted with STATA) to calculate the required sample size. To detect a small-to-medium effect size (Cohen’s *f* = 0.20) in a pairwise comparison of pre-post change between two active treatment arms, with a power of 0.80 and a within-person correlation coefficient of 0.50, 68 participants are needed in this study (34 per arm). We expect 30% of the participants as early drop-outs of the study [56], therefore a total of 105 participants will be included in the study.

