## Statistical analysis

An intention-to-treat analysis will be included in the data analyses of the primary outcome measure (mental wellbeing) and secondary outcome measures (psychiatric functioning, criminal recidivism, substance abuse, quality of life, social network, social support, loneliness and self-sufficiency). Besides, subgroup analyses will be conducted on the protocol completers sample. Generalized Linear Mixed Models (GLMM) in Statistical Package for the Social Sciences (SPSS) will be used to model all continuous outcome measures, considering the distributional characteristics of the data. If the normal distribution assumption is violated, resampling methods will be used to transform data into a normal distribution or appropriate non-parametric tests will be used. Generalized Estimating Equations (GEE) will be used to analyze the categorical outcome measures. The main between-group effect (TAU versus FNC) and the interaction effect (group * time) will be analyzed whilst correcting for baseline assessment. Outcome data of all assessments will be included in the analyses to examine the differences in the development in time between both groups. The criminal recidivism data will be analyzed using Survival Analysis and corrected for time at risk. Missing data will be addressed using multiple imputation or statistical techniques that control for missingness-at-random.

To assess the magnitude of treatment effects on the primary outcome and secondary outcomes, Cohen’s *f* effect size will be calculated. Effect sizes of *f* = 0.40 are considered large, effect sizes of *f* = 0.25 are considered moderate and effect sizes of *f* = 0.10 are considered small (Cohen, 1988).

Moderator analyses will be used to examine potential moderators of treatment outcome by adding potential moderators as covariates of factors to the GLMM/GEE analyses. Furthermore, multilevel mediation models will be carried out to examine potential mediators of treatment outcome. At last, appropriate statistical methodology in ATLAS.ti will be used for the analyses of the qualitative data [111].

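### The rule for non-normal data cannot be carried out as written, and its non-parametric alternative lets the primary estimand change after the open-label data are seen

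*Protocol article*

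**What the plan says.** Two sections of the protocol article give a rule for non-normal data.

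- **Sample size**, on the MHC-SF score: "Normality of the distribution will be checked after data collection using optimal scaling or scatter plotting". It continues: "When the assumption of normality is violated, resampling methods will be used to transform the data into a normal distribution". No other route is offered there.
- **Statistical analysis**, on the continuous outcomes: if normality fails, "resampling methods will be used to transform data into a normal distribution or appropriate non-parametric tests will be used".

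The analysis that this rule would modify is set out in two places. The Primary outcome measure section makes the between-group mean difference in MHC-SF score from baseline to 12 months the main outcome. The Statistical analysis section assigns generalized linear mixed models, which "will be used to model all continuous outcome measures, considering the distributional characteristics of the data". It then states: "The main between-group effect (TAU versus FNC) and the interaction effect (group * time) will be analyzed whilst correcting for baseline assessment". It also states: "Outcome data of all assessments will be included in the analyses to examine the differences in the development in time between both groups". On incomplete data: "Missing data will be addressed using multiple imputation or statistical techniques that control for missingness-at-random".

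The Design section calls the trial open label. The Randomization and procedure section says that patients, therapists and researchers will not be blinded.

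**The concern.** Bootstrap and permutation methods build a reference distribution for an estimate or a test statistic. Neither turns skewed observations into normal ones. An analyst who follows the text literally has nothing to carry out. Any attempt to produce normal data by resampling would mean altering the data, and standard errors from altered data have no clear interpretation.

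The check that triggers the rule is also misdirected. Optimal scaling assigns numerical values to categories; it does not diagnose normality. A scatter plot of the outcome does not show normality either. The mixed model's assumption concerns its residuals and random effects, not the distribution of the raw score.

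The added alternative raises a different problem. The common rank tests do not estimate a mean difference, do not adjust for baseline and give no group-by-time effect. If one of them replaced the mixed model for the primary outcome, the trial would answer a different question from the one it set. That choice would be made after data collection by a team that knows the allocation.

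**Working it through.** The plan gives no figure for this rule, so there is none to reproduce. The check has three parts.

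**1. Does resampling normalise data?** Draws with replacement come from the empirical distribution of the sample, so they carry its shape. Only the distribution of the *mean* over resamples approaches normality, with skewness of about (sample skewness)/√n.

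Inputs: n = 105 (Sample size section); a gamma-type score with shape 1.5 (an assumption, chosen only to be visibly skewed); 2,000 bootstrap samples.

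| Quantity | Result |
|---|---|
| Skewness of the original sample | 1.32 (Shapiro p about 3 × 10⁻⁶) |
| Mean skewness of the bootstrap samples | 1.20 |
| Bootstrap samples with Shapiro p < 0.05 | 99% |
| Skewness of the 2,000 bootstrap means | 0.11 |

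The last row agrees with 1.32/√105 = 1.32/10.25 = 0.13. The small fall from 1.32 to 1.20 is finite-sample behaviour of the skewness statistic, not normalisation: a gamma sample (shape 1) of 5,000 with skewness 1.94 gave 1.95 over 50,000 redraws.

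**2. Do the two sections agree, and do they keep the estimand?**

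| | Sample size | Statistical analysis |
|---|---|---|
| If non-normal | Resampling only | Resampling, or non-parametric tests |
| Rule for choosing between them | Not applicable | None given |
| Baseline-adjusted 12-month mean difference kept? | Not said | Not said for the non-parametric route |

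The sections differ from each other, and neither ties the alternative to the planned contrast.

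**3. What would a switch cost?** Inputs: two-sided alpha of 0.05 ("given an alpha of 0.05 (two-tailed) and a power of 0.80", stated with the first power calculation); within-person correlation 0.50; 34 per arm from the sample size, or 52 per arm from 105/2 = 52.5 rounded down; Cohen's f = 0.20, which for two equal arms is d = 2f = 0.40. Each setting had 4,000 replicates, one baseline and one follow-up, and no dropout. The skewed data used the same assumed gamma shape. Entries are rejection rates.

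| Per arm | Data | Effect | Mann-Whitney, follow-up | Mann-Whitney, change | Baseline-adjusted ANCOVA |
|---|---|---|---|---|---|
| 34 | normal | none | 0.057 | 0.050 | 0.056 |
| 34 | skewed | none | 0.048 | 0.047 | 0.050 |
| 52 | normal | none | 0.051 | 0.055 | 0.055 |
| 52 | skewed | none | 0.047 | 0.051 | 0.046 |
| 34 | normal | d = 0.40 | 0.34 | 0.34 | 0.45 |
| 34 | skewed | d = 0.40 | 0.53 | 0.44 | 0.46 |
| 52 | normal | d = 0.40 | 0.51 | 0.50 | 0.63 |
| 52 | skewed | d = 0.40 | 0.73 | 0.61 | 0.62 |

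Each test alone holds its level (0.046 to 0.057). The rank test on follow-up scores is weaker than ANCOVA with normal data and stronger with skewed data. The cost of a switch is therefore not a predictable loss of power. It is a change in what is estimated and tested.

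**The case against.** The strongest reply is that the resampling sentences are a badly worded bootstrap clause. Because resampled data cannot be made normal, the only workable implementation is bootstrap or permutation inference, which is close to what is recommended below. That may well be what was meant, but both sections state the transformation and neither mentions an interval or test for the treatment contrast. The error is in what the article states, so it is not something merely left to an analysis plan.

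Other parts of the reply stand:

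- The non-parametric tests are unnamed, and rank-based ANCOVA and longitudinal rank methods exist. A reader might infer that the baseline-adjusted repeated-measures analysis *will* be abandoned. The text only permits this. Naming a specific test could fairly be left to an analysis plan.
- A reader might infer that the fallback would use completers only and lose the 30% expected to drop out. The Statistical analysis section separately commits to intention-to-treat and to multiple imputation or missing-at-random methods, and limits neither to the mixed model. Rank tests can be run on imputed data.
- A reader might cite a variance penalty of 1/(1 − 0.5²) = 1.33 for losing baseline adjustment. That is a normal-theory ratio for mean differences, not a property of rank tests, and the rule applies only when data are not normal.
- The mixed-model clause already allows for the distribution of the data, so suitable distributions and links are available. The normality condition in that section follows directly after the model and could refer to residuals. The criticism of the check therefore rests on the Sample size section.
- Any distribution check has to follow data collection. The timing is a problem only because the result can change the estimand.

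**Conclusion.** The point holds in a limited form. The resampling rule is technically wrong in both sections and cannot be executed. The normality check in the Sample size section does not address the model's assumption. The non-parametric alternative in the Statistical analysis section leaves the primary estimand open to change after unblinded data are available.

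No numerical bias is claimed. The simulations found each test's type I error near 0.05 and power differences in both directions, so neither false-positive inflation nor a definite loss of power or patients is supported. They rest on an assumed gamma shape, a single follow-up and no dropout. They did not model the bounded MHC-SF score, the full mixed model or the effect of choosing a test after seeing the data. Nothing in the article indicates how skewed the MHC-SF score will be. That resampling leaves the shape of the data unchanged depends on none of these assumptions.

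This should be corrected before analysis. It does not affect the design or the sample size.

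**What to change.** Replace the resampling sentences in both sections and the normality-check sentence in the Sample size section with one consistent rule:

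- The baseline-adjusted mixed model on the original MHC-SF scale is the primary analysis in all cases, and its 12-month contrast is the primary estimate.
- Model residuals are inspected with Q-Q and residual plots. The result does not change the primary analysis.
- A bootstrap confidence interval is reported for the same 12-month contrast, resampling whole participants, with all their visits, within arm and site. It is best reported always, beside the model-based interval, so that no data-dependent trigger is needed. State in advance which of the two intervals carries the primary inference. Three sites and two arms make six cells, 105/6 = 17.5 patients on average, so also state in advance what is done if a cell is very small.
- Any rank-based analysis is a sensitivity analysis only.
- Skewed count outcomes use a suitable distribution and link (for example negative binomial), as the mixed-model clause already permits.

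The cost is a change of wording and a short bootstrap run. No data collection, design feature or sample size changes.

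### The requirement of 68 participants does not follow from its stated inputs; if f = 0.20 means d = 0.40, 34 per arm gives about 37% to 47% power for the 12-month contrast

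*Protocol article*

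**What the plan says.** All of the sizing is in the Sample size section of the protocol article.

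- Expected effect: "we expect a small to medium improvement of mental well-being in the FNC condition compared to TAU", which the section calls realistic and clinically meaningful.
- First calculation (G*Power), at f = 0.20, "given an alpha of 0.05 (two-tailed) and a power of 0.80". Its result is reported as follows: "indicated that 150 participants are needed (75 per arm").
- Reason for replacing it: "Since this power calculation did not account for the repeated measures design of the study".
- Second calculation (STATA), at the same f. The contrast is described as "0.20) in a pairwise comparison of pre-post change between two active treatment arms". The remaining inputs and the result are then reported: "with a power of 0.80 and a within-person correlation coefficient of 0.50, 68 participants are needed in this study (34 per arm").
- Drop-out is put at 30%, and "therefore a total of 105 participants will be included in the study".

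Two other sections matter. Primary outcome measure names the between-group difference in mental wellbeing from baseline to 12 months as the main outcome. Statistical analysis gives the benchmarks for f: 0.10 is small, 0.25 moderate and 0.40 large (the middle one reads "0.25 are considered moderate and effect sizes of").

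**The concern.** The second calculation cuts the requirement from 150 to 68 at the same f and the same power. The only new input is a within-person correlation of 0.50. In a two-point comparison of change, that correlation brings no gain over a plain comparison of post-treatment scores, so a saving of more than half cannot come from it.

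At stake is how the primary result will be read. A reader who accepts 80% power for a small-to-medium effect will take a non-significant 12-month difference as evidence against such an effect. The article's discussion of challenges and limitations does not mention limited power.

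**Working it through.** **Inputs.** f = 0.20, power 0.80, rho = 0.50, 30% drop-out (Sample size); 1:1 allocation (Randomization and procedure). Two-sided alpha 0.05 is stated for the first calculation only and is assumed for the second.

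**Scale of f.** For two equal groups d = 2f. The article's benchmarks 0.10 / 0.25 / 0.40 then correspond to d = 0.2 / 0.5 / 0.8, the usual small, medium and large. So f = 0.20 is d = 0.40.

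**Trying to reproduce 68.** The normal approximation is n per arm = 2(1.960 + 0.842)² × V / d², with V the variance in units of the outcome variance. At V = 1 this is 2 × 7.849 / 0.16 = 98.1. Power and the exact n use the noncentral t distribution.

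| Analysis at d = 0.40, rho = 0.50 | V | n per arm, 80% power | Power at 34 per arm |
|---|---|---|---|
| Change score, baseline to 12 months | 2(1 − 0.5) = 1.00 | 99 (z), 100 (t) | 0.369 |
| Baseline-adjusted (ANCOVA) | 1 − 0.5² = 0.75 | 74 (z), 75 (t) | 0.467 |

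Simulation gave 0.373 and 0.463. Neither row gives 34.

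**Other readings.**

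- *One-sided alpha 0.05:* 78 per arm (change score) or 59 (ANCOVA); power at 34 per arm is 0.50 or 0.60.
- *f as a within-between interaction in repeated-measures ANOVA, two measurements:* noncentrality is f² × N × 2 / (1 − rho) = 0.04 × N × 4 = 0.16N. 80% power needs N = 52; N = 68 gives 0.90. The same noncentrality in a two-group test of change (SD of change = 1) is N × δ² / 4, so δ² = 0.64 and δ = 0.8 SD.
- *Mean of all five follow-ups with baseline adjustment, compound symmetry:* V = (1 + 4 × 0.5) / 5 − 0.25 = 0.35, so n = 98.1 × 0.35 = 34.3, or 35 (z) to 36 (t) after rounding. Power is 0.78 at 34 per arm. This assumes the full 0.40 SD effect at every visit from month 3 to month 18.
- *Linear slopes over all six visits:* 33.6 per arm, if the difference is 0.40 SD at month 12 and grows to 0.60 SD at month 18.
- *Working backwards:* with 34 per arm, 80% power needs a difference of about 0.69 SD in change. To get there from d = 0.40, rho would have to be about 0.83 (change score) or 0.81 (ANCOVA).

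**The first calculation.** A plain two-group test at f = 0.20 needs 100 per arm, 200 in total. At d = 0.40, 75 per arm gives such a test power of only 0.68. It corresponds to a variance of 0.75, which is what one baseline measure at rho = 0.50 buys.

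**Drop-out.** 68 / 0.70 = 97.1, so 98. Conversely, 105 × 0.70 = 73.5 completers, or 36 to 37 per arm.

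**What 105 delivers after 30% loss.**

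| 12-month contrast | Power at d = 0.40 (36 / 37 per arm) | Difference with 80% power (36.75 per arm) |
|---|---|---|
| Change score | 0.388 / 0.397 | 0.66 SD (f = 0.33) |
| Baseline-adjusted | 0.489 / 0.500 | 0.57 SD (f = 0.29) |

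Both detectable effects lie above the article's own moderate benchmark of f = 0.25.

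**The case against.** **The meaning of f.** The section does not define f for the second calculation. Under the interaction convention, 68 is more than enough for 80% power, so the direction of the error depends on the convention. This stands, and the 37% to 47% must be stated as conditional on d = 2f. It does not rescue the text: 68 at power 0.80 is still not reproduced, and a 0.8 SD difference in change does not fit the effect described.

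**The planned model.** Statistical analysis specifies a mixed model on all assessments, with a group main effect as well as group by time. With a constant 0.40 SD effect over five follow-ups, power is about 0.78 at 34 per arm and 0.82 at 36 to 37. So a reader might infer that every planned test has less than 50% power; the documents do not support that. But the constant effect is optimistic here: coaching preferably starts within two months after baseline, and its first three to six months go to motivation and alliance. Nor is an average over follow-ups the pre-post comparison described, or the 12-month main outcome.

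**How 150 was obtained.** A reader might infer that the first calculation did use repeated measures, because 150 matches a two-measurement between-factor test at rho = 0.50. The article gives no number of measurements or correlation for it, and other settings also give 150. The documents show only that the description and the figure do not agree.

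**The total of 105.** It exceeds the 98 that 68 would require. The mismatch is on the safe side, and no other derivation of 105 is documented.

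**Conclusion.** The point holds in conditional form. The figure of 68 is not obtained from f = 0.20, rho = 0.50 and power 0.80 for a pairwise comparison of pre-post change under any two-point reading tried.

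Assuming d = 2f, two-sided alpha 0.05 and the single baseline-to-12-month contrast, the requirement is about 100 per arm (change score) or 75 (ANCOVA), against 34 stated. Models using all visits come close to 34 per arm under favourable assumptions; if one was used, the section describes it wrongly. Either way the text needs correction, because the trial relies on the stated power.

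The account of the 150 figure needs reconciling but is not shown to be false. The drop-out arithmetic is a minor point.

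**What to change.** Keep 105 and correct the Sample size section:

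1. Restate the power, for example: *With 105 randomised and 30% loss (about 36-37 per arm), the trial has 80% power for a 12-month difference of about 0.57 SD (baseline-adjusted) or 0.66 SD (change score); power for d = 0.40 (f = 0.20) at 12 months is about 49-50% or 39-40%.*
2. For the second calculation, state the definition of f, alpha and its sidedness, and the assessments used. Give any higher power claimed for the all-assessment model together with its assumptions on the course of the effect and the correlation.
3. Reconcile the statement that the 150 calculation ignored repeated measures with the 200 that a plain two-group test at f = 0.20 needs, by giving that calculation's inputs.
4. Note that 68 with 30% drop-out gives 98, and that 105 is a margin above it.
5. Add to the limitations that a non-significant 12-month result does not exclude a small-to-medium effect.

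This costs a few sentences and no extra patients. The stated power for the main contrast becomes less favourable.
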